### Stopping rules

Twelve months after initiating the trial, we will conduct an interim analysis at a two-sided *P *< 0.01 level. If the results indicate no trend toward a change (increase or reduction) in antibiotic treatment (curtailment from 48 to 24 hours) in prophylactic empirical therapy, and if there is no trend at the *P *< 0.1 level toward improved secondary outcomes, then the trial will be discontinued. The interim analysis implies that the result of the final analysis should be considered significant if *P *< 0.04.

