### Objectives and hypotheses

Our objectives are to achieve a clinically relevant reduction in overall antibiotic use and to reduce treatment costs caused by delayed diagnosis of nosocomial infection. In this study we will test the hypothesis that routine surveillance by determination of cytokine levels in plasma and tracheal aspirates will allow safe discontinuation of antibiotic therapy within 24 hours if the proposed laboratory prediction model indicates absence of infection. We regard a reduction in antibiotic exposure by 15% to be a clinically relevant effect. The second hypothesis we will test is whether early diagnosis reduces the morbidity and costs associated with hospital acquired infection. Ascertaining relevant indicators of morbidity and costs in all patients with culture proven bloodstream infection will operationalize this.

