### Measures of outcome

The primary outcome measure is the rate of systemic antibiotic use per 1000 days of hospitalization (see details under Sample size calculation and statistical considerations). Secondary outcome measures are as follows (for all episodes of hospital acquired infection with positive blood cultures for the first 7 days following initiation of antibiotics after adjusting for important possible patient confounders): number of days free from mechanical ventilation (an indicator of respiratory failure); number of days free from inotropic support (an indicator of circulatory failure); costs for specific expensive medications (e.g. fresh frozen plasma); and nurse allocation (an indicator of treatment intensity).

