### Sample size calculation and statistical considerations

At present, in the ICU antibiotic therapy is employed in 40% of patients, which represents a decline from our original survey conducted in 1998 (up to 80% of all patients) [3]. The expected reduction in antibiotic usage is 10–25%, with a clinically relevant reduction considered to be any reduction in excess of 10%. The minimum number of days of hospitalization in each arm required to detect a 10% reduction with a type I error under 5% and a power of 80% is 2300. The expected follow up rate is in excess of 90%. Because the unit of randomization is days and not individuals, an unknown intracluster (intraday) correlation coefficient must be considered. The standard χ^2 ^statistic, which assumes independence of individuals, may not be applicable. We may be forced to acknowledge the nested nature of the data (clustered randomized controlled trial) by using test statistics based on the generalized linear mixed model [12]. To safeguard against insufficient power we believe that the sample size must be increased to 25%, leading to a required accrual of 3000 hospitalization days per arm. Given the size of the participating units, this translates to a study duration of 24 months.

All analyses will be carried out on an intention-to-treat basis. This means that any antibiotic treatment course will be allocated according to the randomization status of the day on which the decision to withhold or to continue had to be made. This requires us to perform three subgroup analyses: antibiotic prescription prevalence according to the day's randomization status; antibiotic free days following the 4 days after any microbiological work up; and antibiotic free days during the week following any initiation of antibiotics.

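### The 12-month stopping rule treats absence of an undefined 'trend' as futility, and the power calculation makes no allowance for it

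*Protocol article*

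**What the plan says.** The Stopping rules section sets one interim analysis at 12 months, at two-sided P<0.01. The only action it states is discontinuation, which is mandatory when two conditions hold together. The first begins "If the results indicate no trend toward a change (increase or reduction) in antibiotic treatment (curtailment from 48 to 24 hours" and refers to prophylactic empirical therapy. The second is that no secondary outcome shows an improving trend at P<0.1. The section then adds "The interim analysis implies that the result of the final analysis should be considered significant if" P<0.04.

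Under Measures of outcome, "The primary outcome measure is the rate of systemic antibiotic use per 1000 days of hospitalization". The Sample size section gives the hospitalization days per arm "required to detect a 10% reduction with a type I error under 5% and a power of 80% is 2300", raises this to 3000 for clustering by day, and arrives at 24 months. It also says "The expected reduction in antibiotic usage is 10–25"%, while the Objectives section says "We regard a reduction in antibiotic exposure by 15% to be a clinically relevant effect".

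**The concern.** A test at half the data is often non-significant when the planned effect is real, so non-significance there is weak evidence of futility. A mandatory stop on that basis can end a trial of a strategy that works.

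The wording adds four problems:

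- No level is attached to the antibiotic condition. The paragraph offers 0.01 (for the interim analysis) and 0.1 (for the secondary outcomes), and the choice between them changes the risk greatly.
- The condition has no direction. A trend toward more antibiotic use prevents stopping, although the aim is a reduction.
- Nothing is said to happen if P<0.01 is reached, yet the final test pays for that look.
- The sample size was inflated for clustering only, so the stated power takes no account of the rule.

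**Working it through.** **Inputs.** Control rate 40% ("At present, in the ICU antibiotic therapy is employed in 40% of patients"), a 10% relative reduction to 36%, and "with a type I error under 5% and a power of 80"%. Equal arms and a two-sided test are assumed. The interim is at 12 of 24 months, so the information fraction t = 0.5 is also an assumption.

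**The plan's own figure.** n = [1.960·√(2·0.38·0.62) + 0.842·√(0.40·0.60 + 0.36·0.64)]² / 0.04² ≈ 2311 days per arm, which agrees with 2300. The relative, two-sided reading is therefore the one the plan used.

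**Antibiotic condition alone.** The drift at the final analysis is 1.960 + 0.842 = 2.802. At the interim the mean of Z is 2.802·√0.5 = 1.981.

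- Trend means P<0.1: P(|Z|<1.645) ≈ Φ(1.645 − 1.981) = Φ(−0.336) ≈ 37%.
- Trend means P<0.01: P(|Z|<2.576) ≈ Φ(2.576 − 1.981) = Φ(0.595) ≈ 72%.

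**Adding the secondary condition.** The trial stops only if no secondary outcome trends. As an illustration, assume four independent secondary outcomes with no effect, also independent of the antibiotic result. With a 5% chance each, the chance of any trend is 1 − 0.95⁴ = 18.5%. With 10% each it is 1 − 0.90⁴ = 34.4%. The stopping probability is the first condition times one minus this chance.

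**Power.** Power comes from simulating the interim and final Z values as bivariate normal with correlation √0.5. Success is P<0.01 at the interim or P<0.04 at the end. Counting P<0.01 as success is itself an assumption, since the article does not say so. Without a futility stop, power is 77.8%.

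| Meaning of 'trend' | Chance of a secondary trend | Stopped | Power |
|---|---|---|---|
| P<0.1 | 0 | 37% | 59% |
| P<0.1 | 18.5% | 30% | 62% |
| P<0.1 | 34.4% | 24% | 65% |
| P<0.01 | 0 | 72% | 28% |
| P<0.01 | 18.5% | 59% | 37% |
| P<0.01 | 34.4% | 48% | 45% |
| P<0.5 | 0 | 9% | 75% |

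**Sensitivity of the antibiotic condition (P<0.1 / P<0.01).**

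- True 15% reduction, 2300 days per arm: drift 0.06/√((0.24 + 0.2244)/2300) = 4.222, interim mean 2.985, giving 9% / 34%.
- True 25% reduction: drift 7.149, interim mean 5.055, giving about 0% / 0.7%.
- 3000 days per arm with a design effect of 1.25: 35% / 71%. With 3000 independent days: 27% / 62%.
- The Setting section gives 5500 hospitalization days a year. If all counted, t = 5500/6000 = 0.917 and the interim mean is 2.802·√0.917 = 2.68, giving 15% / 46%.

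**Overall type I error.** Levels of 0.01 at half information and 0.04 at the end give about 0.045.

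**The case against.** A reader might infer that the rule would stop 37–72% of trials with a real effect. The article does not support that. The two conditions are joined by 'and', so these figures describe the antibiotic condition alone and are a ceiling on stopping.

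A reader might also infer that the rule works at a stated significance level. It does not: the antibiotic clause has none. The P<0.01 reading is the less natural one, because a trend usually means something short of significance and the same sentence uses P<0.1 for it. A looser reading costs little.

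Nor does the rule do away with the planned 80% power. It reduces it, by an amount that depends on the reading, and the 0.04 final level alone already brings it to about 77%. The article also expects reductions of up to 25%, for which the loss is small or nil, and half information is not certain. The chance range for a secondary trend assumes no secondary effect, although the trial hypothesises one; with a 50% chance of a secondary trend, power would be 68% (P<0.1) or 53% (P<0.01).

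Finally, the remark about curtailment from 48 to 24 hours may only describe the expected mechanism, so it does not prove that the interim variable differs from the primary outcome.

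All of this narrows the size of the problem. The undefined threshold, the missing direction, the missing action at P<0.01 and the silent power calculation remain. The secondary outcomes are also a weak safeguard, because they are counted only in hospital-acquired, culture-positive episodes.

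**Conclusion.** The concern holds in this form: the rule is mandatory, uses lack of a trend as futility, and leaves the decisive threshold open. Taken over all the readings tried, the same sentence allows power between about 28% and 75% for the 10% reduction that the trial is sized to detect, against about 78% with no futility stop. Under the more natural P<0.1 reading, 24–37% of such trials would be stopped and power would be 59–65%.

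These figures rest on half information at 12 months, the drift behind 2300 days per arm, and, for the adjusted range, the assumed chance of a secondary trend. They are smaller for true 15–25% reductions or a later information fraction. The rule should be rewritten before the 12-month results are seen.

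**What to change.** Replace the paragraph with a rule on the primary outcome, antibiotic days per 1000 hospitalization days:

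1. State that two-sided P<0.01 at the interim is the efficacy boundary, and what follows if it is crossed.
2. Delete the 'no trend' and P<0.1 criteria. Use instead a non-binding futility guideline in the direction of reduction, for example conditional power below 20% under the planned 10% reduction. At half information the boundary is z = (2.054 − 2.802·0.5 − 0.842·√0.5)/√0.5 ≈ 0.08. Recompute it at the actual information fraction; at 0.917 the same formula gives (2.054 − 2.802·0.083 − 0.842·√0.083)/√0.917 ≈ 1.65.
3. Keep the final level at 0.04. Raising it to 0.045 would bring the overall error to about 0.050 and leave no margin.
4. Restate power as about 78%, or enlarge the sample if 80% is required.

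The 20% cut is one reasonable choice; the essentials are a defined threshold, a direction and a stated action. At half information the guideline stops 2.9% of trials with a true 10% reduction and costs under 0.5 points of power (77.8% to 77.5%). The downside is that a trial with no effect stops at 12 months only about 53% of the time. With no secondary trend, the present rule would stop 90% or 99% under the P<0.1 or P<0.01 reading, though only 50% under the P<0.5 reading.

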**Methods:**

All patients admitted to the multidisciplinary neonatal and paediatric intensive care unit of a university children's hospital will be included. Patients will be allocated either to routine sepsis work up or to the intervention strategy with additional cytokine measurements. Physicians will be requested to estimate the pre-test probability of sepsis and pneumonia at initial suspicion. In the treatment arm, physicians will receive raw cytokine results, the likelihood ratio and the updated post-test probability. A high post-test probability will suggest that immediate initiation of antibiotic treatment is appropriate, whereas a low post-test probability will be supportive of watchful waiting or discontinuing prophylactic empirical therapy. Physicians may overrule the suggestions resulting from the post-test probability.

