To assess the clinical efficacy of the new diagnostic measures, we suggest that a randomized controlled trial be conducted comparing two management strategies. The control strategy will consist of routine management, with the exception that physicians are requested to provide a probability estimate for the presence of bacterial infection whenever a diagnostic work up (blood cultures or tracheal aspirate culture) is ordered. The intervention strategy will consist of cytokine measurement from the sample and provision of a result based post-test probability within a few hours after sample collection. The null hypothesis states that the management arms will not differ with respect to antibiotic utilization rate, measured as the number of days on systemic antibiotic treatment per 1000 days of hospitalization. The secondary null hypothesis states that the arms will not differ with respect to costs associated with hospital acquired septic shock.

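### The antibiotic condition in the 12-month discontinuation rule is worded as earlier stopping of empirical therapy, not as the primary outcome on which the trial is sized

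*Protocol article*

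**What the plan says.** The Introduction states the null hypothesis for the antibiotic utilization rate, "measured as the number of days on systemic antibiotic treatment per 1000 days of hospitalization". Measures of outcome repeats it: "The primary outcome measure is the rate of systemic antibiotic use per 1000 days of hospitalization". Objectives and hypotheses aims at overall antibiotic use, and the sample size section works from overall use (40% at present, 10% reduction).

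Stopping rules uses other terms. "Twelve months after initiating the trial, we will conduct an interim analysis", and the antibiotic condition is the absence of a trend toward a change, upward or downward, in "antibiotic treatment (curtailment from 48 to 24 hours) in prophylactic empirical therapy". A second condition is joined to it by *and*: there must also be no trend at P<0.1 "toward improved secondary outcomes, then the trial will be discontinued". The primary rate is not named anywhere in that section.

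**The concern.** The strategy can change antibiotic use by more than one route. According to the Abstract, "a low post-test probability will be supportive of watchful waiting or discontinuing prophylactic empirical therapy", and a high probability supports starting treatment at once. The Intervention strategy section adds continuing treatment when infection is indicated. The intention-to-treat paragraph assigns courses by the day on which withholding or continuing was decided. Courses never started, courses added and courses prolonged all count in a rate of systemic antibiotic days. None of them is a shortening of empirical therapy from 48 to 24 hours.

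Two mismatches could follow:

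- The antibiotic condition for discontinuation may be met while the primary outcome is moving as planned, because part of the saving comes from withheld courses.
- The condition may fail to be met, because curtailment is clear, while added treatment cancels the saving in the primary outcome.

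The first is the more costly. If the secondary outcomes also show no trend, a trial on course for its primary aim would end after 12 of its 24 planned months.

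**Working it through.** **1. Which quantity the trial is sized on.** Inputs from the sample size section: control rate 0.40, relative reduction 10% (so 0.36), type I error 5%, power 80%.

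n per arm = [1.96·√(2·0.38·0.62) + 0.8416·√(0.40·0.60 + 0.36·0.64)]² / 0.04² = (1.3454 + 0.5772)² / 0.0016 ≈ 2311.

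The article states 2300, so its figure reproduces on overall antibiotic use with a two-sided test.

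**2. The measures side by side.**

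| Event | Primary rate | Antibiotic condition as worded |
|---|---|---|
| Empirical course stopped at 24 instead of 48 hours | counts | counts |
| Course withheld | counts | does not count |
| Course added on a high probability | counts | does not count |
| Course prolonged | counts | not as curtailment, although the rule also speaks of an increase |

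**3. Illustration of the divergence.** Assumptions not in the article:

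- Half of the planned 3000 days per arm has accrued at 12 months (1500).
- Days are independent.
- A trend means two-sided P<0.1. The article attaches that level only to the secondary outcomes.
- A share w of the planned saving comes from withheld courses.
- Curtailment is measured over all hospital days.

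The visible difference is d = 0.04·(1 − w), with p0 = 0.40 and p1 = 0.40 − d.

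z = d / √[(p0·q0 + p1·q1)/n]; P(no trend) = Φ(1.645 − z) − Φ(−1.645 − z).

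- Primary outcome, d = 0.04: z = 0.04/√(0.4704/1500) = 2.26; P(no trend) = 27%.
- Curtailment, w = 1/4, d = 0.03: z = 0.03/√(0.4731/1500) = 1.69; P(no trend) = 48%.
- Curtailment, w = 1/2, d = 0.02: z = 0.02/√(0.4756/1500) = 1.12; P(no trend) = 70%.

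**4. Sensitivity.** If all 5500 annual days in the Setting section counted, each arm would have 2750 days at 12 months. The three figures become 8%, 26% and 55%. If curtailment is instead measured on empirical days only, taken as 20% falling to 18% of days (assumed, with w = 1/2), P(no trend) is 60% with 1500 days and 40% with 2750.

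**5. The opposite direction.** If a share f of antibiotic days is empirical and every such course is halved, overall use falls by 0.5·f. At f = 20% this is exactly the 10% reduction. Below 20%, complete curtailment would still fall short of it. The article does not give f.

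**The case against.** **The parenthesis may be a loose gloss.** The rule speaks of an increase or a reduction, which fits antibiotic treatment in general better than curtailment. Objectives and hypotheses names discontinuation within 24 hours as the expected mechanism. This reading is possible, so the text is ambiguous and does not firmly define a curtailment endpoint. However, the restriction to prophylactic empirical therapy still narrows it, and the looser reading needs the same clarification.

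**Curtailment alone does not decide.** A reader might infer that the trial can be stopped simply because no curtailment is seen. The text does not support this, because the secondary outcomes must also show no trend. That limits the consequence but does not cure the mismatch: the secondary outcomes are not the primary rate either, and they are confined to hospital-acquired infections with positive blood cultures.

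**The size is driven by assumption.** This stands. The Intervention strategy section mentions only stopping or continuing. Withholding appears in the Abstract and in the attribution rule, with no share given. If all the saving were earlier stopping, curtailment over all days would do as well as the primary outcome. On a narrower base it could do better: for 20% to 16% of days with 1500 per arm, z = 0.04/√(0.2944/1500) = 2.86 and P(no trend) is about 11%.

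**The error split.** A reader might infer that the interim 0.01 is spent on the wrong endpoint and wrongly charged to the final test. The article says "we will conduct an interim analysis at a two-sided *P *< 0.01 level" without naming an endpoint, and that "the result of the final analysis should be considered significant if *P *< 0.04". The interim test may well be of the primary outcome, and 0.01 + 0.04 = 0.05 is then in order. No error in the split is shown.

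**Continuing is harmless to validity.** This is also correct. Running on to 24 months does not bias the final test, and a futility look does not inflate type I error. The cost of wrongly continuing is time and resources.

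**A journal article condenses.** It does, but here the article states a criterion that differs from its own primary outcome, so this is more than an omitted detail.

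**Conclusion.** The point holds in limited form. The antibiotic condition of the discontinuation rule, as worded, is narrower than the primary outcome. Neither of the two joined conditions is the primary outcome, and the wording conflicts with itself on direction. The two measures can therefore give different answers at 12 months.

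The mismatch itself rests on the text. Its size does not: 27% against 48% or 70% is an illustration under assumed withholding shares, 1500 independent days per arm and an assumed trend level. The figures describe the antibiotic condition alone, and the joint rule stops less often. Clustering by day, which the article itself raises as a possibility, would push all three upward. Even on the primary outcome, 27% is not small, so the fix aligns the rule with the trial's aim without making the interim look decisive.

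The change should be made. It does not call the final analysis into question.

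**What to change.** Reconcile Stopping rules with the Introduction and Measures of outcome. Name the rate of systemic antibiotic days per 1000 hospital days, with the same attribution rule as the final analysis, as the antibiotic endpoint of both the interim test and the discontinuation rule. Report curtailment of empirical courses as a descriptive process measure that does not enter the decision. This concerns the endpoint definition only and changes no treatment rule.

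The cost is about one sentence. The primary outcome is already collected, and the sample size and the 0.01/0.04 split remain as they are. The small downside is that the interim decision loses a measure more specific to the mechanism stated in Objectives and hypotheses.

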## Discussion

A variety of publications report excellent diagnostic performance of new markers of infection [13,14]. However, a theoretically useful test may not necessarily provide clinically useful information. Most test accuracy studies derive their results from a subgroup of potentially eligible patients who satisfy unanimously accepted criteria for acceptance as cases or controls. Unfortunately, this practice suffers from the potential overestimation of the test accuracy [15] and, even more importantly, it disregards any clinical information that is available apart from that pertaining to the test under question.

In this randomized controlled trial we wish to assess the clinical efficacy of an innovative diagnostic procedure for the diagnosis of bacterial infection in newborns and critically ill children. It will evaluate whether this strategy results in a clinically relevant reduction in overall antibiotic usage, and whether the strategy is cost-effective by reducing treatment costs caused by delayed diagnosis of nosocomial infection.

One of the possible limitations of the study is the required extended study duration of 24 months. It is conceivable that experience gained from patients in the intervention arm or other factors attributable to the conduct of the study (for example increased awareness by physicians because of more conscious decision making) will also affect the control arm. This might lead to an altered prescription pattern in the control group, which would reduce our ability to find a significant difference between the study arms.

If the new test proves efficacious in clinical practice and is cost-effective, then it may become established as a routine marker of infection in this specific setting.

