## Key messages

• 	Test accuracy should be evaluated prospectively with integrated bedside clinical information.

• 	The presented design of this ongoing RCT addresses these demands and shall test whether an innovative diagnostic procedure results in a relevant reduction in unnecessary antibiotic utilization and whether this new strategy proves to be cost effective.

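### The economic conclusions are broader than the cost outcomes: selected drug costs and nurse allocation in culture-positive episodes cannot show cost-effectiveness

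*Protocol article*

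**What the plan says.** The economic aim appears in several places in the protocol article.

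- Introduction: "The secondary null hypothesis states that the arms will not differ with respect to costs associated with hospital acquired septic shock".
- Objectives and hypotheses: one objective is to lower the treatment costs that follow late diagnosis of nosocomial infection. The second hypothesis is about morbidity and costs of hospital-acquired infection, and is made concrete as follows: "Ascertaining relevant indicators of morbidity and costs in all patients with culture proven bloodstream infection will operationalize this".
- Discussion: the trial will evaluate "whether the strategy is cost-effective by reducing treatment costs caused by delayed diagnosis of nosocomial infection". The section ends by tying uptake to the answer: "If the new test proves efficacious in clinical practice and is cost-effective, then it may become established as a routine marker".
- Key messages: the trial is to test "whether this new strategy proves to be cost effective".

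Measures of outcome limits every secondary outcome to one setting, "for all episodes of hospital acquired infection with positive blood cultures for the first 7 days following initiation of antibiotics". Four measures follow: ventilator-free days, inotrope-free days, "costs for specific expensive medications (e.g. fresh frozen plasma"), and nurse allocation as a marker of treatment intensity. Only the third is expressed as a cost.

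The data sources under Data collection match this list: database costs of specific medications by patient and day, and staff allocation. Control strategy states that control specimens are not assayed. Intervention strategy states that intervention specimens are.

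**The concern.** A conclusion on cost-effectiveness has to set what the strategy costs against what it changes, in all the patients to whom it is applied. Here the strategy is applied at every work-up, but its economic consequences are read only in culture-positive hospital-acquired episodes, and there only through some drugs and an uncosted staffing indicator. The price of the test is not among the listed items.

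The Discussion makes adoption of the marker depend in part on this result, so a reader could take a favourable drug-cost comparison in a small subset as the economic case for routine use.

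The secondary null hypothesis has a related problem. It names septic shock costs, but no outcome identifies septic shock. A result for bloodstream infection could be reported as the answer to a different question.

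**Working it through.** **1. Figures available.** The plan gives no figure for any cost outcome, so there is none to reproduce. Its one sample size, 2300 days per arm, belongs to the antibiotic outcome. With 40% against 36% (a 10% relative reduction), two-sided 5% and 80% power:

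n = [1.96 × √(2 × 0.38 × 0.62) + 0.8416 × √(0.40 × 0.60 + 0.36 × 0.64)]² / 0.04² ≈ 2311.

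That agrees with 2300, but says nothing about costs. The check below is therefore one of scope.

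**2. Claim against measurement.**

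- *Population.* The claim concerns the strategy as a whole. The measurement covers hospital-acquired episodes with positive blood cultures. The Introduction says that only a minority of treated patients are truly infected, and that ventilator-associated pneumonia is the unit's commonest reason for antibiotics. Pneumonia without a positive blood culture, and work-ups in uninfected patients, fall outside every cost outcome.
- *Items.* The claim concerns cost-effectiveness. The measurement covers specific expensive drugs, plus nurse allocation, which is not stated to be costed.
- *Cost of the strategy.* Assay cost is zero in the control arm and wholly incremental in the intervention arm. It appears in no outcome and no data source. In the pilot, fewer than one third of episodes had a potentially useful result, so more than 1 ÷ (1/3) = 3 episodes were tested per useful result. The trial was then narrowed to suspected infection, so its yield may differ. The pilot does show that testing is not confined to episodes in which it helps.

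**3. What the omissions do.** Write the true cost difference, intervention minus control, as D = A + P + N, where

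- A is assay cost, greater than 0;
- P is the difference in treatment costs in culture-positive hospital-acquired episodes;
- N is the difference in all other work-ups, including the culture-negative ones.

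The plan measures M, which is part of P. The error is

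M − D = −A − N − (P − M).

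Leaving out A makes the strategy look cheaper than it is. If the strategy shortens antibiotic courses in uninfected patients, as intended, the drug part of N is negative, and leaving it out makes the strategy look dearer. The sign of M − D depends on A, N and P − M. The article gives no assay price, number of tests or number of bloodstream infections, so neither the sign nor the size can be computed.

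**4. Septic shock.** The Introduction's hypothesis concerns costs of septic shock. The Objectives put culture-proven bloodstream infection in its place, and Measures of outcome uses culture-positive hospital-acquired infection. The nearest thing to shock is inotrope-free days, described as reflecting circulatory failure. That is a morbidity measure, not a cost, and it does not define which episodes were shock.

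**The case against.** Several points on the other side have force.

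- The first Discussion statement explains what it means by cost-effective: lower treatment costs from late diagnosis. This nearly repeats the Objectives, and the listed outcomes do bear on that narrower question. This stands. The overreach lies in the unqualified Key messages statement and in the Discussion's closing sentence on routine use.
- Septic shock is not wholly unmeasured, because inotrope-free days is a partial proxy. This stands, and leaves a mismatch between hypothesis and outcome rather than a complete gap.
- An article may leave test costing to a fuller document, and nothing says that assay costs will be excluded. This stands in part. Silence on a unit price would be no finding. But the outcomes are listed explicitly, and the conclusions in the same article go beyond them.
- The article sets no rule for declaring cost-effectiveness. True, but it makes adoption conditional on the answer.

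A reader might infer that the omissions bias the comparison in favour of the intervention, since the assay is left out. The documents do not support this: savings in culture-negative work-ups are left out too. A reader might also set the number of assays against the number of culture-positive episodes and ask how much each episode must save to break even. That would need rates the article does not give, and would charge every assay to culture-positive episodes while ignoring any saving elsewhere.

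**Conclusion.** The point holds as a mismatch between stated conclusions and stated outcomes. The listed outcomes can support a statement on selected treatment costs in culture-positive hospital-acquired episodes over 7 days. They cannot support a conclusion that the strategy is, or is not, cost-effective. The net error is of unknown size and direction. The secondary null hypothesis also needs to be brought into line with the population in which it will be tested.

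This rests on the outcome list as printed and assumes that no separate economic evaluation exists elsewhere. The primary outcome, the allocation and the sample size are unaffected. The correction should be made because the economic conclusion is among the article's headline aims.

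**What to change.** Choose one of two routes.

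1. **Widen the comparison.** Compare the available medication costs and staff allocation over all worked-up episodes by allocated status, and add a unit cost for each assay performed. Keep culture-positive episodes as a subset. Start the window at the work-up, since not every work-up leads to antibiotics; the study nurse already records clinical data in both arms from the day before culture to 6 days after. Report the result as a partial cost comparison, because the database is described as holding costs of specific medications and not total costs.
2. **Narrow the claim.** In the Discussion and Key messages, limit the conclusion to selected treatment costs in culture-positive episodes and remove the term cost-effective.

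On either route, reword the secondary null hypothesis in the Introduction to the population used under Objectives and Measures of outcome.

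The first route costs a modest extra analysis and one laboratory unit price. The second costs only wording and a narrower claim.
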